### Sample size

The sample size of this study is calculated for the primary endpoint of group difference in the RMDQ at 12 months. According to literature, results obtained after interarcuair decompression should be 3 points lower on the RMDQ compared with those for the laminectomy group in order to detect superiority.^45^

Hence, the sample size of this study is based on a superiority design, using a delta of 3, an assumed true mean difference of 0 and a pooled SD of 6. Using an alpha of 0.05, and a power of 90%, we calculated a sample size of 69 patients per group. Accounting for a 20% loss in follow-up, we will therefore enrol 174 patients (87 patients per group).

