### Data collection methods

All patient reported outcomes will be collected preoperatively and after 3 weeks, 6 weeks, 3 months, 6 months, 12 months, 18 months, 24 months, 36 months and 48 months (see table 1). Patients will receive an email with a link, reminding them of the upcoming data collection and requesting them to fill in the web-based questionnaires. If the questionnaires are not completed, the patient will receive a reminder after 1 and 2 weeks. After 2 weeks, non-responders will be contacted by phone.

**Table 1 T1:** Participant timeline schedule

Table	Visit plan and case report forms											
	Intake	Surgery (t_0_)	1–2 day(s) following surgery	FU 3 weeks	FU 6 weeks	FU 3 months	FU 6 months	FU 12 months	FU 18 months	FU 24 months	FU 36 months	FU 48 months
Visit surgeon	x				x							
Research nurse visit	x				x			x		x		x
Randomisation		x										
Surgery		x										
Discharge			x									
Physical examination	x				x			x		x		x
Functional X-rays	x				x					x		
Roland-Morris Questionnaire	x			x	x	x	x	x		x	x	x
Oswestry Disability Index	x			x	x	x	x	x		x	x	x
NRS leg and back pain	x			x	x	x	x	x		x	x	x
Patient self-received recovery and satisfaction	x			x	x	x	x	x		x	x	x
EuroQol-5D	x			x	x	x	x	x		x	x	x
Cost questionnaires	x			x	x	x	x	x	x	x		
Short form 36	x			x	x	x	x	x		x	x	x
Revisit and complications	With occurrence											

FU, follow-up; NRS, Numeric Rating Scale.

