### Statistical analysis

Patient characteristics will be summarised per treatment group to determine whether the randomisation was balanced. Continuous variables will be presented using means and SDs, or in the case of non-normally distributed variables using medians and IQRs. Normality will be graphically assessed. Categorical variables will be presented using counts and percentages. The primary analysis will study differences in the primary outcome measure (RMDQ). The primary endpoint of interest is 12 months after randomisation. The results of the RMDQ will be assessed using generalised linear mixed models (GLMM), to account for the repeated measurements within patients and the multicentre stratification.

The secondary outcomes (ODI, NRS leg and back pain score, TUG test, TCST and the SF-36) will be similarly assessed using GLMMs and will be analysed for exploratory purposes. In all analyses the primary assessment of treatment effect will be the estimate of the main effect within the appropriate model at 12 months, adjusted for the stratification factors and main covariates. Time to recovery will be analysed using survival analysis (Cox proportional hazards). At 24, 36 and 48 months, the GLMM repeated-measurement analyses using the compound symmetry covariance structure will be used while *group* (interarcuair and conventional), *time* (moments of measurement) and the *interaction* between group and time (grou×time) will be entered as independent variables. Dependent variables are the primary and secondary outcome parameters. Likert scales for self-reported patient recovery and satisfaction will be assessed using descriptive statistics (counts and percentages) and appropriate plots. Comparisons of Likert scale results at individual time points will be tested using Mann-Whitney U tests. Complications and incidence of reoperations will be assessed using descriptive statistics (counts and percentages). Comparisons between treatment groups for specific complications of interest will be assessed using Χ^2^ tests or Fisher’s exact tests. If necessary, missing data will be imputed using multiple imputation techniques.

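### The long-term models fix a compound-symmetry covariance over visits from 3 weeks to 48 months; if correlation falls with lag, the group-by-time test and early-versus-late contrasts are anticonservative

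*Protocol article*

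**What the plan says.** The Statistical analysis section separates two stages. For the primary stage it states "The primary endpoint of interest is 12 months after randomisation" and calls for a generalised linear mixed model, without naming a covariance structure. For the later stage, at 24, 36 and 48 months, it does name one: "the GLMM repeated-measurement analyses using the compound symmetry covariance structure will be used". Group and time are in the model, and the interaction "between group and time (grou×time) will be entered as independent variables". The scope is wide: "Dependent variables are the primary and secondary outcome parameters". The secondary outcomes "will be analysed for exploratory purposes".

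Data collection methods places the patient-reported outcomes preoperatively and "after 3 weeks, 6 weeks, 3 months, 6 months, 12 months, 18 months, 24 months, 36 months and 48 months". Table 1 shows no RMDQ at 18 months, which leaves eight RMDQ follow-ups: 3 and 6 weeks, and 3, 6, 12, 24, 36 and 48 months. The only variability figure is in the Sample size section: "using a delta of 3, an assumed true mean difference of 0 and a pooled SD of 6".

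**The concern.** Compound symmetry requires the 3-week and 6-week scores to be as strongly correlated as the 3-week and 48-month scores, and requires the same variance at every visit. Gaps between consecutive visits run from 3 weeks to 12 months. Scores taken close together usually correlate more than scores taken years apart. The Introduction also expects courses to diverge, through instability after laminectomy or residual stenosis after the limited procedure.

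If correlation falls with lag, the model pools all pairs into one average correlation. That average is too high for distant visits, so the model understates the variance of a change between an early and a late visit. Those changes are what the group-by-time interaction tests, so a claim that the two operations diverge over the long term could rest on a test with more than its nominal error rate.

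**Working it through.** **1. The plan's sample size, used here as an input.** With SD 6, delta 3, alpha 0.05 and power 90%, n = 2·6²·(1.645 + 1.282)²/3² = 68.5, so 69 per group. This reproduces the plan's figure with a one-sided alpha (two-sided gives 85). Allowing for 20% loss, 69/0.8 = 86.25, so 87 per group and 174 in total. Complete-data checks below use 69 per group and drop-out checks use 87.

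**2. Assumptions.** All correlations are assumed, because the article gives none. Two families were used:
- calendar-time decay: ρ(lag) = f + (s − f)·exp(−lag/τ), with lag and τ in months;
- AR(1) by visit order: ρ = r^(number of visits apart).

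**3. Size of the group-by-time test.** With complete data this test under compound symmetry is the univariate repeated-measures F test, referred to F with 7 and 7·(2·69 − 2) = 952 degrees of freedom. Its true null distribution is [Σλⱼχ²₁/7] / [Σλⱼχ²₁₃₆/(7·136)], where λⱼ are the seven non-zero eigenvalues of the covariance matrix centred over visits. Each line below uses 200,000 draws with constant SD 6.

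**4. Standard error of the 48-month minus 3-week contrast.** With complete data and constant SD, model SE/true SE = √[(1 − ρ̄)/(1 − ρ(3 weeks, 48 months))], where ρ̄ is the mean of the 28 pairwise correlations. For AR(1) 0.85: √[(1 − 0.637)/(1 − 0.321)] = 0.73.

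| Assumed truth | ρ 3–6 weeks | ρ 3 weeks–48 months | ρ̄ | Test size | Early–late SE ratio |
|---|---|---|---|---|---|
| Compound symmetry 0.5 | 0.50 | 0.50 | 0.50 | 5.0% | 1.00 |
| f 0.35, s 0.60, τ 12 | 0.59 | 0.35 | 0.43 | 5.5% | 0.94 |
| f 0.4, s 0.8, τ 12 | 0.78 | 0.41 | 0.53 | 6.6% | 0.89 |
| f 0.3, s 0.8, τ 12 | 0.77 | 0.31 | 0.46 | 6.9% | 0.88 |
| f 0, s 0.8, τ 36 | 0.78 | 0.21 | 0.49 | 8.0% | 0.81 |
| f 0.2, s 0.85, τ 24 | 0.83 | 0.29 | 0.53 | 8.1% | 0.82 |
| AR(1) 0.7 | 0.70 | 0.08 | 0.41 | 8.7% | 0.81 |
| AR(1) 0.8 | 0.80 | 0.21 | 0.55 | 9.6% | 0.76 |
| AR(1) 0.85 | 0.85 | 0.32 | 0.64 | 10.0% | 0.73 |
| AR(1) 0.9 | 0.90 | 0.48 | 0.74 | 10.5% | 0.71 |

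Other calendar-time patterns tried gave 5.4% to 8.6%. An SE ratio q gives an error rate of 2Φ(−1.96q), so 0.94 to 0.71 means about 7% to 17% for the early-versus-late contrast.

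**5. Standard error of the 48-month difference alone.** With complete data, model SE/true SE = √(mean variance/variance at 48 months).
- Constant SD: 1.00.
- SD rising from 5 to 7 in equal steps over eight visits: mean variance 36.43, √(36.43/49) = 0.86, error 9%.
- SD falling from 7 to 5: √(36.43/25) = 1.21, error 2%.

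**6. Drop-out.** The setting is generalised least squares with a compound-symmetry working covariance, monotone drop-out completely at random, and 20% or 35% lost by 48 months. Under decaying correlation, the 48-month ratio is:
- constant SD: 0.92 to 0.98 (error 5.6% to 7.2%);
- SD rising from 5 to 7: 0.80 to 0.84 (error 10% to 12%);
- SD falling from 7 to 5: 1.08 to 1.17 (error 2% to 3%).

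The group-by-time test then runs at about 6% to 13% across these scenarios.

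**The case against.** **The size rests on assumptions.** This stands. A reader might infer that the test's error rate doubles. Only strong serial decay (AR(1) by visit order of about 0.8 to 0.9), or decay combined with rising variance and drop-out, gives that. Decay towards a lasting patient-level correlation of 0.3 to 0.4 gives under 7%.

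**Late-visit standard errors are not simply too small.** This also stands. A reader might expect narrow error bars at 24, 36 and 48 months in every case. With constant SD and complete data they are correct, and with falling variance they are too wide. The article's single pooled SD cannot settle the direction.

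**The primary analysis is out of reach.** This stands too. Extending the criticism to 12 months is tempting, but the article names compound symmetry only for the later analyses and places the main assessment of treatment effect at 12 months. The secondary outcomes are exploratory, and the interaction is entered as a model term without being named as a decision test.

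**Fewer visits, less effect.** For the 24-month RMDQ analysis (six follow-ups) the same calculation gives about 5% to 9%. For the timed tests, which have four postoperative visits, it gives 5.0% to 5.6% under calendar-time decay and about 6% to 7% under AR(1).

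**A separate analysis plan may add detail.** Absence of a fallback or of robust standard errors from a condensed article is no defect. The structure itself, however, is stated. The provision for multiple imputation, if needed, does not answer the point either: completed data analysed with compound symmetry still give the test sizes in step 3.

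**Conclusion.** The point holds for the long-term analyses. A restrictive covariance is fixed for a visit schedule it suits poorly. In every decaying pattern tried with complete data and constant SD, the eight-visit group-by-time test exceeded 5%, by a little (about 5.5%) or by a factor of about two (10.5%). Early-versus-late standard errors were about 0.7 to 0.95 of the true value. Single-visit standard errors at 48 months may be right, too small or too large, depending on how variance and drop-out develop. All of this is conditional on correlations and SDs that the article does not give; if compound symmetry is true, the test runs at 5.0%. Nothing here shows an effect on the 12-month primary conclusion.

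**What to change.** In the sentence on the 24, 36 and 48 month analyses, replace the compound-symmetry structure with an unstructured covariance over visits, fitted by REML with Kenward-Roger degrees of freedom. State that, if this does not converge, a simpler heterogeneous structure will be used with empirical (sandwich) standard errors.

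The change is to wording only and touches no visit, patient or sample size. An unstructured matrix has 8·9/2 = 36 parameters for eight visits, which is feasible with 174 patients. If compound symmetry happens to hold, a little efficiency is lost. The unstructured model also frees the handling of drop-out from a single assumed correlation.

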### Allocation

Computerised block randomisation will take place after the patient has been anaesthetised. Allocation concealment will be assured by using ALEA, a web-based data system supervised by the Clinical Trial Centre of the Erasmus MC. Variable block sizes of 4, 6 and 8 will be used and stratified by treatment centre. Patients will be randomised in a 1:1 ratio to laminectomy or bilateral interarcuair decompression. Each patient will be given a unique study number.

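### Recovery and satisfaction are compared with unstratified Mann-Whitney tests although randomisation is stratified by centre: valid, but some power may be lost

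*Protocol article*

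**What the plan says.** Under Allocation, the article uses computerised block randomisation, 1:1, "stratified by treatment centre". Study setting/population lists three centres, all in Rotterdam.

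The Statistical analysis section then treats outcomes in two ways.

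- **Modelled outcomes.** The RMDQ is analysed with a generalised linear mixed model (GLMM) that accounts for repeated measurements and centre. Next comes "The secondary outcomes (ODI, NRS leg and back pain score, TUG test, TCST and the SF-36) will be similarly assessed using GLMMs", described as exploratory. Recovery and satisfaction are not in that list. The following sentence defines the treatment effect as the "main effect within the appropriate model at 12 months, adjusted for the stratification factors and main covariates".
- **Recovery and satisfaction.** "Likert scales for self-reported patient recovery and satisfaction will be assessed using descriptive statistics (counts and percentages) and appropriate plots". The formal comparison follows: "Comparisons of Likert scale results at individual time points will be tested using Mann-Whitney U tests". No stratified form is named.

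Two further provisions bear on these scales. Time to recovery has a Cox model, and missing data may be multiply imputed if necessary. For the GLMM at 24, 36 and 48 months the article says: "Dependent variables are the primary and secondary outcome parameters". Recovery and satisfaction both stand under the Secondary outcomes heading.

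**The concern.** When randomisation is balanced within centres, the arms cannot differ much in their centre mix, so the true sampling variability of the treatment comparison excludes most of the between-centre variation. An unstratified Mann-Whitney test still counts that variation in its variance. If centre predicts the answer on the scale, the variance is too large for the design: the test rejects less often than 5% under the null and has less power under an alternative.

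The trial has already paid for stratification and uses it in its modelled analyses. Leaving it out for patient-perceived recovery, one of the secondary outcomes named in the abstract, gives away precision that could be kept at no cost in data.

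There is also a question of wording. Read literally, the sentence on dependent variables places the same Likert scales in a repeated-measures model at 24, 36 and 48 months, while the rank test is assigned to them as well. Nothing says which result leads.

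**Working it through.** **The plan's own figure.** No figure is stated for the Likert comparisons. The sample size section gives 69 per group for the RMDQ (difference 3, SD 6, power 90%), and 174 in total after 20% loss. With one-sided alpha 0.05, n = 2 × (1.645 + 1.282)² × 6² / 3² = 68.5, so 69; then 69 / 0.8 = 86.25, so 87 per group and 174 in total. (Two-sided alpha would give 85 per group. That is a separate matter and does not affect this point.) The 69 is used here only as the number per arm expected to be available.

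**The two tests.** With ranks r in a sample of N patients, n₁ and n₀ per arm, and W the rank sum of one arm:

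- Mann-Whitney: z = (W − n₁(N + 1)/2) / √V, with V = n₁n₀ / (N(N − 1)) × Σ(r − r̄)², ranking all centres together.
- Van Elteren: rank within each centre i, then z = Σ wᵢ(Wᵢ − Eᵢ) / √(Σ wᵢ²Vᵢ), where Eᵢ is the null expectation of Wᵢ and wᵢ = 1/(Nᵢ + 1).

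**Simulation on the logit scale.** Assumptions: a logistic latent variable cut into 7 categories; three centres with 28, 23 and 18 patients per arm (sum 69); common odds ratio 2; two-sided 5%. Centre sizes, centre effects and the odds ratio are assumed, because the documents give none. Three separate runs of 3000, 6000 and 4000 simulated trials gave this power (Mann-Whitney vs van Elteren):

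| Centre effects | 3000 trials | 6000 trials | 4000 trials |
|---|---|---|---|
| none | no loss | 63.7% vs 63.3% | 62.9% vs 62.7% |
| ±0.5 logit | 59.7% vs 61.2% | 61.1% vs 63.4% | 60.9% vs 63.3% |
| ±1.0 logit | 51.3% vs 61.1% | 53.1% vs 61.8% | 53.5% vs 62.1% |

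The losses are 1.5, 2.3 and 2.4 points at ±0.5 logit, and 9.8, 8.7 and 8.6 points at ±1.0 logit. At ±1.0 logit the type I error was 3.4% vs 4.7% (3000 trials) and 3.6% vs 5.5% (6000 trials).

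**Hand check at ±1.0 logit.** For three equal centres at −1, 0 and +1, the between-centre variance is 2/3 = 0.667. The logistic variance is π²/3 = 3.290. The unstratified statistic is shrunk by about √(3.290 / 3.957) = 0.912, so the effective critical value is 1.96 / 0.912 = 2.15 and the type I error is about 2 × (1 − Φ(2.15)) = 3.2%, close to the simulated values.

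**Different assumptions, same direction.** A second simulation used 174 patients, permuted blocks of 4, 6 and 8 within centre, 20% random loss, a normal latent variable, a treatment shift of 0.5 SD and 4000 trials per setting. Mann-Whitney vs van Elteren:

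| Centre means | Power, centres 58/58/58 | Power, centres 100/50/24 | Type I, 58/58/58 | Type I, 100/50/24 |
|---|---|---|---|---|
| no difference | 80% vs 80% | 80% vs 80% | 4.9% vs 5.0% | 5.3% vs 5.6% |
| ±0.25 SD | 79% vs 80% | 78% vs 79% | 4.5% vs 4.4% | 5.0% vs 5.3% |
| ±0.5 SD | 74% vs 78% | 75% vs 78% | 3.6% vs 4.3% | 4.4% vs 5.5% |
| ±1 SD | 56% vs 77% | 60% vs 76% | 1.7% vs 5.3% | 2.6% vs 4.7% |

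One logistic SD is 1.81 logits, so the ±1 SD row is a wider spread than anything in the first table.

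**Reading of the results.** In no setting did ignoring centre materially inflate the type I error. When centres are alike, the stratified test has practically the same power.

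**The case against.** The strongest reply is that an unstratified rank test is valid here and the choice is one of preference. The test supplements a mainly descriptive analysis of outcomes that did not size the trial. A loss worth noticing needs large centre differences: ±1.0 logit means an odds ratio of e² ≈ 7.4 between the extreme centres, and nothing in the documents suggests that for three Rotterdam centres sharing eligibility criteria and procedures. A condensed article may also leave such detail to the full protocol or SAP. Most of this stands and sets the weight of the point. It does not remove it: the article names a specific test, and the stratified version costs nothing where the objection is right and helps where it is wrong.

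A reader might infer more than the documents support:

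- **A firm contradiction.** The article says "In all analyses the primary assessment of treatment effect will be the estimate of the main effect within the appropriate model at 12 months", and it requires this estimate to take centre into account. Taken literally, the rank test breaks that rule. But the sentence directly follows a GLMM list that omits recovery and satisfaction, and it speaks of an effect within a model. It can fairly be read as covering only the modelled outcomes.
- **A risk of false positives.** The error goes the other way.
- **Results reported only as p values.** Counts, percentages and plots are planned, and the Cox model gives recovery an effect measure. Satisfaction has no interval stated, but it is not left without a size.
- **Patients with a missing visit are dropped.** Multiple imputation is allowed if necessary, with no exception for these scales.
- **No lead time point.** Twelve months is the stated endpoint of interest. If the sentence on adjusted effects is taken to cover the Likert scales, it also gives them 12 months.
- **Twenty-four tests.** Three scales at the eight post-operative visits in Table 1 give 3 × 8 = 24, but the text refers to individual time points, not to every visit. This is a ceiling, and it has no bearing on stratification.

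**Conclusion.** The point holds as a minor one. The named test ignores the factor by which patients are randomised, while the modelled analyses in the same section use it. The consequence is possible conservatism and lost power on secondary outcomes; validity is not affected. Under the logit-scale assumptions above, the loss runs from about nil to about 9 to 10 percentage points. The upper end depends on a centre spread for which the documents give no evidence, so the true loss may well be negligible.

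Separately, the sentence on dependent variables leaves the Likert scales with two assigned analyses at 24, 36 and 48 months. This is an ambiguity of wording, to be settled by stating the intention.

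**What to change.** Replace the Mann-Whitney U test for recovery and satisfaction with its centre-stratified (van Elteren) version at the same time points. This is one change of wording, needs no new data, and on the figures above costs essentially nothing in power if centres do not differ.

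A proportional-odds mixed model with centre, giving a common odds ratio with a 95% confidence interval, is an optional alternative. Its price is the proportional-odds assumption, which would have to be checked.

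Also state whether the secondary outcome parameters in the 24, 36 and 48 month GLMM include the Likert scales. If they do, say which analysis leads at those visits; if not, restrict the sentence to the outcomes already listed for GLMM analysis.

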### Economic evaluation

An economic evaluation will be performed from the societal and healthcare perspectives to evaluate the cost-effectiveness of the bilateral interarcuair decompression compared with a ‘classic’ laminectomy for patients with INC. When the societal perspective is applied, all costs and consequences relevant to the interventions will be taken into account, whereas only costs accruing to the formal Dutch healthcare sector will be considered when the healthcare perspective is applied. Intervention costs will be estimated using a micro-costing approach. Cost questionnaires will be administered at 3, 6 and 12 weeks covering the entire period and at 6, 12, 18, 24, 36 and 48 months after surgery covering the previous 3 months. Data will be collected on healthcare utilisation, the use of informal care, absenteeism, presenteeism and unpaid productivity losses. Costs will be valued using guideline prices recommended in the Netherlands.^46^

A cost-utility analyses will be conducted with QALYs as outcome. For estimating QALYs, the patients’ EQ-5D-5L health states will be converted into utility scores using the Dutch tariff.^43^ Linear interpolation between measurement points will be used to subsequently calculate QALYs. Missing data will be imputed using multiple imputation by chained equations.^47^ An incremental cost-utility ratio will be calculated by dividing the difference in costs by the difference in effects. The cost-utility ratio expresses the incremental costs per QALY gained. Bootstrapping techniques will be used to estimate the uncertainty surrounding the cost-effectiveness estimates. Uncertainty will be shown in cost-effectiveness planes and cost-effectiveness acceptability curves, and sensitivity analyses will be performed to test the robustness of the study results.

